#### Health Care Providers

Participating FHTs will identify 1 occupational therapist from their site to participate in the study. This HCP will both administer the research protocol and participate in semistructured, in-depth interviews and questionnaires. To be eligible to participate, the HCP must have the approval to participate from the appropriate corporate agent (the Executive Director of the FHT). Before starting data collection, the HCP must complete a web-based training program—consisting of 3 self-directed training modules—and learn how to administer the Qmci to become a certified BrainFx administrator. The research team will conduct in-person training to cover the research protocol and administrative processes.

#### FHT Administrative Executives

Where available, the managing director or equivalent at the FHT will be interviewed to better understand contextual factors such as workload, funding, and patient population characteristics that may impact the results.

### Ethics and Consent

The study protocol has been reviewed and has received ethics clearance from the Wilfrid Laurier University Research Ethics Committee (ORE# 5820) and has been reviewed and approved through each FHT’s research approval process. All participants (HCPs, patients, care partners, and administrative executives) will read and sign an information and informed consent package before participating in the study. We will conform to recommendations for acquiring informed consent and conducting qualitative interviews with persons with dementia when recruiting patients who may be affected by a neurocognitive disease [78-80]. During oral informed consent, we will use plain language, repeat information that is not understood, and ask the participant to explain their understanding of what the study entails. During the interview, we will use plain language; be prepared to repeat questions as needed and ask questions in a different way, possibly using the participant’s own words to rephrase; allow participants ample time to respond to each question; and provide cues to what they were saying if they lose train of thought. If they dwell overly long on a particular question, we will validate the meaningfulness of their response, gently redirect them to the next question, monitor for fatigue, and allow them to continue the interview at another time. Participants will be informed that they can choose not to answer the questions asked to them. All participants will be assigned a study participation number, and when reporting, identifying information will be removed from verbatim quotes if approval has been provided for use.

### Measures

#### The 10-Item GAS

The GAS-10 is a 10-item self-report screen for anxiety in older adults [81] developed for rapid screening of anxiety in clinical settings (GAS-10 is the short form of the full 30-item GAS [82]). The screen includes 10 questions taken directly from the GAS that measure somatic (ie*, I felt tired*), cognitive (ie*, I could not control my worry*), and affective (ie, *I was irritable*) symptoms of anxiety that reflect those used to diagnose anxiety disorder in the *Diagnostic and Statistical Manual of Mental Disorders*, fourth edition, text revision. Participants will be asked to use a 4-point Likert scale (0=not at all, 1=sometimes, 2=most of the time, and 3=all of the time) to rate how often they have experienced each symptom during the past week, including the day of the visit [82]. The GAS-10 has a maximum score of 30, with higher scores indicating higher levels of anxiety [81-83]. Although 3 subscales have been identified, the GAS-10 is reported to be a unidimensional scale of general anxiety [84,85]. Validation of the GAS-10 suggests that it is optimal for assessing average to moderate levels of anxiety in older adults, its total and subscale scores are highly and positively correlated with the GAS, and it possesses high internal consistency [81]. This tool will assess the patients’ anxiety level as it relates to screening for cognitive impairment at the time of the assessment and any change in subjective ratings after completion of the MCI screen and between visits. Although the association between neuropsychological assessment anxiety and test performance is unclear [86,87], the inclusion of a pre-post anxiety measure will allow researchers to control this issue and to explore any variation in performance or anxiety related to tablet technology. Given the exclusion criteria for this study (Table 1), we do not anticipate high levels of nontest anxiety.

#### The SCREEN

The SCREEN (version 0.5, beta) will be administered on a tablet (ASUS ZENPAD 10.1“ WXGA IPS Display, 1920×1200), powered by a quad-core 1.5 GHz, 64-bit MediaTek MTK 8163A processor with 2 GB RAM and 16 GB storage. The tablet comes with a tablet stand for optional use and a dedicated stylus that is recommended for completion of a subset of activities. At the start of the study, HCPs will be provided with identical tablets, preloaded with the BrainFx app software for use for the duration of the study.

Using a standardized administration protocol developed by BrainFx, the HCP will instruct the patient to use either their finger or the provided stylus to complete the SCREEN. Following acclimation to the tablet, the patient will be required to complete a short survey to collect demographic information (eg, age, the highest level of education attained) and any history of pre-existing conditions and questions about the patients’ state of well-being at the time of testing (eg, self-reported concerns about their thinking, mood, hours slept, and pain). The questionnaire will be immediately followed by 7 activities that are modeled after everyday real-world actions purported to evaluate functional competence related to a variety of cognitive domains, including abstract reasoning, divided attention, or visual-spatial abilities (refer to Table 1 for a detailed description of the activities). Tasks will be timed and digitally scored, and an activity score for each activity will be generated based on a combination of the patients’ accuracy (ie, number of correct responses) and processing speed (ie, speed of completion). The relative weight that accuracy and processing speed contribute to the activity score is proprietary to BrainFx and is the same for each of the 7 activities.

At the end of each SCREEN, the patient will be prompted by the app to consent to contribute their scores to a database of results maintained by BrainFx, known as the LBB. The mean and SD of the LBB database will be updated in response to the addition of every new SCREEN. The patient’s performance on the SCREEN will be evaluated by comparing their results with the global reference population (ie, all available SCREEN results in the LBB at the time of testing). Filters are available that allow the HCP to compare the patients’ results with subcohorts using factors such as gender, education, age, or primary diagnosis. Individual SCREEN results reports display the individual’s activity score, the LBB mean (for the global reference population unless the operator selects subcohorts based on selected filters), and whether the activity score falls within 1 SD of the LBB mean. If the patient’s activity score falls 1 or more SD below the global mean, it is classified as an *area of challenge*. The HCP is instructed to use their clinical judgment to interpret the results by applying any number and combination of filters relevant to the patient. For the purpose of this study, the patient’s performance will be compared against all results in the LBB completed by people aged 55 years and older at the time of testing.

#### The Qmci Screen

The Qmci is a sensitive and specific screen that differentiates normal cognition from MCI [63,65]. The HCP will administer the screen by asking the patient questions and recording their response on a dedicated Qmci assessment form provided by the screen developers. The patient will be required to answer 1 question via paper and pencil. The Qmci takes approximately 5 minutes to complete, is scored by hand out of 100 points, and evaluates 6 cognitive domains: orientation (10 points), registration (5 points), clock drawing (15 points), delayed recall (20 points), verbal fluency (20 points), and logical memory (30 points) [68]. The overall cut-off score to distinguish normal cognition from MCI on the Qmci is ≤67, from cognitive impairment (MCI or dementia) ≤62, and dementia alone ≤54 [88]. Although not as broadly adopted as the MoCA 8.1 in Canada, its psychometric properties, administration time, and availability for use suggest that Qmci is the optimal market assessment tool for MCI screening in FHT settings.

#### The Task Technology Fit Questionnaire

In the Task Technology Fit (TTF) model, technologies refer to any tool(s) used to complete a task, and the task itself is any number of actions performed to complete the task. Operationally, *fit* is defined as the extent to which the technology assists in completing these necessary actions [89,90]. Building on the TTF, Goodhue and Thompson [89] introduced the technology-to-performance chain model to acknowledge, first, that measuring perceived net benefit to use requires that the technology be used to complete the task for which it is designed and, second, to factor in the impact of related social norms or personal attributes on the evaluation of the technology and its utilization. Evidence suggests that the better the fit between the characteristics of the technology and task, the better the impact technology has on performance, which positively influences its utilization [89,90]. TTF models have been used to evaluate technologies across diverse sectors, including health care [91] and education [92], via questionnaires that tap constructs related to the technology, such as perceived satisfaction, reliability, the accuracy of the task, task completion time, ease of use or training, risk, and trust [90]. Across studies, individuals are asked to rate their perspective on the technology using a 7-point Likert scale ranging from entirely disagree (1) to entirely agree (7), and questions are tailored to address the technology and research questions at hand [89].

In this study, the questions on the TTF questionnaire are designed to measure how the SCREEN system (ie, assessment, handouts, hardware, and technical support) influences the HCP’s ability to screen for MCI. Tasks include, but are not limited to, collecting data from the patient that are relevant to MCI and using those data to make necessary decisions (eg, the decision to refer patients for further neuropsychiatric evaluation or provide particular intervention recommendations for MCI [37,51]). HCPs will be asked to rate the SCREEN system according to how the technology impacts the characteristics of their tasks and their ability to perform them, user satisfaction, utilization, and their perceived net benefits to using the tool [89,92].

#### Zarit Burden Interview

Care partners will complete the 12-item Zarit Burden Interview (ZBI) [93] as part of their entry or exit interviews scheduled within 1 month of their partner’s first and last screening appointments. The ZBI is the most common self-report screen used to measure subjective burden reported by people caring for those with chronic health conditions who require, over time, increasing support for managing their day-to-day ADL and IADL (ie, cognitive impairment) [94,95]. The 12-item ZBI [94] is one of several validated short-form screens used for brevity in place of the full 22-item ZBI [96]. The 12-item ZBI is reported to measure 2 dimensions of burden (personal and role strain) [94], is highly and positively correlated with scores on the full 22-item ZBI, presents with high internal consistency, and is a reliable tool for measuring changes in caregiver burden over time [93,94,97,98]. Participants are asked to use a 5-point Likert scale (0=never, 1=rarely, 2=sometimes, 3=quite frequently, and 4=nearly always) to rate how they feel in response to items such as, “Do you feel strained when you are around your relative?” and “Do you feel that your health has suffered because of your involvement with your relative?” [94]. Participants can score a maximum of 48 points, and scores equal to or higher than 17 are classified as a high or severe burden [94,99]. Data from this questionnaire will be used to triangulate the test results, impact, and patient self-reported anxiety.

### Data Collection and Procedures

The summary of the study protocol for the data collection process is included for reference in Figure 1.

**Figure 1 figure1:**
[figure not shown]
Study protocol data collection process. AOC: area of concern; ED: executive director; EMR: electronic medical record; ET: evaluation team; FHT: family health team; GAS: Geriatric Anxiety Scale; HCP: health care provider; IC: informed consent; MCI: mild cognitive impairment; PEF: patient encounter form; Qmci: Quick Mild Cognitive Impairment Screen.

#### Psychometric Evaluation

Data collection for the psychometric evaluation study will take place in person at the patients’ respective FHT. Standard operating procedures have been developed for the research study, which will be followed by the research team and HCP staff trained in the study protocol and administration of all data collection tools. A member of the research team will observe at least one in-clinic HCP data collection visit to confirm adherence to the protocol and training procedures.

To assess the reliability and perceived usefulness of the SCREEN, depending upon when a patient enters the study, they may repeat the screening protocol up to 4 times. Each visit is structured around the administration of 2 MCI screens; the *GAS-10* [81,82]; and a series of questions that measure the patient’s use of technology, change in their general health and well-being, or any interactions with the health care system related to MCI that occur in the 3 months since their last appointment. The HCP will be required to complete a patient encounter form at each appointment, which includes a summary of the patient’s MCI screen results, any referrals, and their responses to these questions.

The patients’ first appointment will take approximately 45-60 minutes (to account for onboarding), and all subsequent appointments (up to 4 screening test pairs, depending on the patient’s study entry date) will take approximately 45 minutes to complete. Rolling recruitment of patients will occur over an 18-month period and will end when a minimum of 2 and a maximum of 4 SCREEN-Qmci test pairs are completed every 12 weeks. In older adults, with no diagnosis of MCI or dementia, measures of cognitive abilities, including verbal fluency, attention, and intelligence [100], and measures of executive functioning [101] remain stable for anywhere from 4 to 8 weeks or from 1 to 5 years between test and retest (controlling for the effects of normal aging [100]). To date, there are no clear guidelines on the optimal time between tests [102,103]. Streiner [104] recommends longer periods to avoid recall bias. Furthermore, greater practice effects are experienced with shorter test-retest intervals [62]. The 3-month interval was therefore selected to minimize such confounds and is justified given the stability of the constructs under investigation. A randomization process will determine the order of screen administration at each visit. The Qmci will be administered using a pen and paper. HCPs will be provided with identical tablets, preloaded with the SCREEN app software.

The GAS-10 will be administered just before and immediately after the administration of the first MCI screen (eg, the SCREEN) and immediately followed by the administration of the second MCI screen (eg, the Qmci) at each appointment. After completing the 2 MCI screens, the HCP will manually calculate the results for the Qmci, log in to the BrainFx portal to retrieve the SCREEN report, and review both sets of results with the patient. The Qmci cut-off score for distinguishing MCI from normal cognition is ≤67/100 [88]. The SCREEN does not include scoring guidelines for a cut-off score but identifies whether a score on any of the 7 tasks is an *area of challenge*.

To determine the sensitivity and specificity of the SCREEN in comparison with the Qmci, the results of both screens will be classified in binary format as healthy or not healthy, where *healthy* denotes SCREEN=no areas of challenge in all 7 activities and Qmci≥67 and *unhealthy* denotes SCREEN=1 or more areas of challenge and Qmci≤67. Consistent with consensus guidelines for screening for cognitive impairment [37,49,50], the research protocol will also require HCPs to refer patients to their primary care physician for further evaluation if they receive an abnormal score on the Qmci or significant concerns on the SCREEN. The SCREEN does not have a standardized cut-off score that can be used to classify results as abnormal. Therefore, in consultation with and on the recommendation of the SCREEN developers, for the purpose of the research protocol, a set of cut-off scores was developed to classify SCREEN results as normal (zero areas of challenge), some concerns (≤3 areas of challenge), or significant concerns (≥4 areas of challenge). All HCPs in this study will be OTs who are trained to assess individuals’ abilities or disabilities through the use of standardized testing and functional observation. As a result, the study protocol includes a condition that referral decisions for physician oversight or further testing are the purview of the HCP and their clinical judgment. This became the proxy gold standard for a positive screen in this research study.

Following the review of the results at each appointment, the HCP will provide patients with a handout that summarizes recommendations for supporting cognitive health. If the SCREEN identifies any *areas of challenge,* the patient will also receive a handout developed by BrainFx containing tailored strategies to strengthen brain health and manage deficits in those areas.

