#### Descriptive and Inferential Analysis

Descriptive data will be described using frequencies and percentiles and compared using the chi-square test or Fisher exact test as necessary. Continuous data will be analyzed for central tendency and variability; categorical data will be presented as proportions. Normality will be tested using the Shapiro-Wilk test, and nonparametric tests will be performed using the Mann-Whitney U test*.* Statistical significance will be considered at a *P* value of .05, with 90% CI provided where appropriate. We powered the exploratory analysis to validate the SCREEN using an estimated effect size of 12%, with the understanding that Canadian prevalence rates are not available [29], and determined that we needed at least 114 participants. For test-retest reliability, using 90% power and a 5% type 1 error rate, we will require a minimum of 58 test results.

MCI test outcome data will be coded into a binary format of *healthy* or *unhealthy* (where unhealthy indicates a positive result on the test, ie, 1 or more *areas of challenge* on the SCREEN results, or a score of ≤67/100 on the Qmci) to account for the difference in categorical versus continuous outcome variables. For this reason, sensitivity and specificity will be determined using cross-tabulation rather than using the area under the curve using receiver operating characteristic curves. A principal component analysis with varimax rotation will be used to better understand the derivation of components’ contribution to screen test outcomes and to explore the differences between a conventional MCI screen (Qmci) and one that is intended to be more ecologically valid by assessing functional impairment (SCREEN). Binary logistic regression will examine the effects of variables such as age, education, self-reported comfort with technology, anxiety before and after completing the MCI tests, and sleep levels on the results. The internal consistency of both the SCREEN and Qmci will be assessed using Cronbach α. Test-retest reliability, the ability of a measurement instrument to reproduce results on 2 or more occasions (ceteris paribus), will be assessed using an intraclass correlation coefficient [106].

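### The retest is not strictly all-else-equal: screen order can switch between visits and score-dependent feedback is given in the interval, so the ICCs and the post-screen anxiety contrasts should account for both

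*Protocol article*

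**What the plan says.** On order, the Psychometric Evaluation section of the protocol article states: "A randomization process will determine the order of screen administration at each visit". Patients have at least two visits, and "they may repeat the screening protocol up to 4 times".

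On feedback, the same section has the provider "review both sets of results with the patient". At each appointment "the HCP will provide patients with a handout that summarizes recommendations for supporting cognitive health". A patient with any area of challenge on the SCREEN also gets a developer handout "containing tailored strategies to strengthen brain health and manage deficits in those areas".

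On the interval, it says: "The 3-month interval was therefore selected to minimize such confounds and is justified given the stability of the constructs under investigation". The reasons given are construct stability, recall and practice effects.

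On the estimand, Descriptive and Inferential Analysis describes test-retest reliability as "the ability of a measurement instrument to reproduce results on 2 or more occasions (ceteris paribus" and assesses it with an intraclass correlation coefficient. Order and handout are not among the variables named for the regression, although that list is open-ended.

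On anxiety, The 10-Item GAS says the scale will assess "any change in subjective ratings after completion of the MCI screen and between visits". Psychometric Evaluation places the GAS-10 just before and just after the first screen of the visit, whichever screen that is.

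**The concern.** An ICC from repeated visits measures the instrument only if the conditions of test and retest match. Two stated procedures change them.

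- **Order.** A patient may take the SCREEN first at one visit and second at the next. Any warm-up, fatigue or anxiety effect of position then becomes within-patient variation and is counted as instrument error.
- **Feedback.** Between visits the patient has seen the results and, if any activity was flagged, holds advice aimed at the activities that will be scored again. Exposure depends on the first SCREEN score, so an effect would change spread and rank as well as the mean.

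The argument for the 3-month interval addresses neither. A low SCREEN ICC would be hard to attribute to the tool alone.

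For anxiety, the post-screen reading follows the tablet at some visits and the paper test at others. A between-visit difference in that reading, or in the pre-post change, can therefore be a difference between tools.

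**Working it through.** **The plan's own figure.** The article requires at least 58 test results at 90% power and 5% type 1 error, without naming the design ICCs. The usual ICC formula is n = 1 + 2k(z_a + z_b)² / [(k − 1)(ln C0)²], with C0 = [1 + k·r0/(1 − r0)] / [1 + k·r1/(1 − r1)]. Take k = 2, one-sided 5%, r0 = 0.70 and r1 = 0.85. Both ICC values appear in the Introduction for the parent instrument, but using them as design inputs is my assumption.

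- C0 = 5.667/12.333 = 0.459, so (ln C0)² = 0.605.
- n = 1 + 4 × 8.564/0.605 = 57.6, that is 58.

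Other input pairs also give 58, so these inputs are plausible but not confirmed. The figure is not shown to be wrong.

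**How often order switches.** With independent 1:1 draws (the article gives no ratio), the chance of at least one change over k visits is 1 − 2 × 0.5^k: 50% for two visits and 87.5% for four.

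**Effect of order on the ICC.** Let d be the difference in score, in SDs, between taking a screen first and second. A random order adds d²/4 to the within-patient variance, so observed ICC = ICC/(1 + d²/4). With a true ICC of 0.85:

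| assumed d | observed ICC |
|---|---|
| 0.2 | 0.85/1.0100 = 0.842 |
| 0.3 | 0.85/1.0225 = 0.831 |
| 0.5 | 0.85/1.0625 = 0.800 |
| 0.7 | 0.85/1.1225 = 0.757 |

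**How many patients get tailored strategies.** The trigger is any of 7 activities at least 1 SD below the reference mean (The SCREEN). If scores are normal and match the reference, the share is about 70% with independent activities, 56% at an inter-activity correlation of 0.3, and 48% at 0.5.

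**Effect of feedback on the ICC.** A simulation of 400,000 patients gave the lowest 70% at visit 1 a gain of g SD at visit 2, with a true ICC of 0.85 and an absolute-agreement ICC.

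| assumed effect | observed ICC |
|---|---|
| g = 0.2, no order effect | 0.818 |
| g = 0.5, no order effect | 0.719 |
| g = 0.2 and d = 0.2 | 0.809 |
| g = 0.5 and d = 0.5 | 0.666 |

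With a consistency ICC, g = 0.2 and g = 0.5 alone give 0.826 and 0.769.

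**Power at n = 58 against 0.70** (same assumed inputs): 90% at an ICC of 0.85, 86% at 0.842, 69% at 0.818, 54% at 0.800 and 9% at 0.719.

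**GAS-10.** The pre-screen reading comes before both screens, so that day's order cannot move it; only earlier feedback can. The post-screen reading and the pre-post change do depend on which screen came first.

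**The case against.** A reader might infer that randomising order at each visit is a design error and that the reliability and anxiety results are contaminated. The documents do not support that.

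- Randomised order is ordinary counterbalancing and protects the SCREEN-Qmci comparison from systematic order bias. In the ICC it adds random error, which biases the estimate downwards, and it can be modelled if order was recorded.
- Varying order serves the stated aim of exploring anxiety related to tablet technology, because some patients then have pre-post readings around both tools.
- No order or feedback effect is given. When the SCREEN comes second, it follows a screen of about 5 minutes and a 10-item scale, so a small order effect is plausible.
- Feedback is not confined to the SCREEN. Both results are reviewed, everyone gets the general handout, and an abnormal Qmci also prompts referral. The handouts are part of the SCREEN system being evaluated.
- Quantitative collection stopped in March 2020 (Results), so a changed randomisation or a new form item cannot help these data. Restricting the main analysis to same-order pairs would leave about 0.5 × 114 = 57 of the planned participants, against a minimum of 58 if that counts patient pairs.
- Restricting the main ICC to patients who did not use the strategies would select on the first SCREEN score.

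All of this stands. What remains is that score-dependent feedback sits poorly with the article's own all-else-equal definition, that order switching adds avoidable error to the ICC, and that the post-screen GAS-10 contrasts need to identify the tool.

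**Conclusion.** The concern holds in a limited form. The retest conditions are not strictly equal, and the analysis described in the article names neither source of inequality.

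The loss from order switching is probably small: 0.85 to 0.84 at an assumed 0.2 SD, reaching 0.80 only at 0.5 SD. Feedback could cost more (0.82 at an assumed 0.2 SD gain, 0.72 at 0.5 SD) and bears mainly on the SCREEN. These figures rest on an assumed true ICC of 0.85, independent 1:1 order draws, and effect sizes that the documents do not supply. They show what may happen, not what did.

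Two stronger conclusions are not supported. The pre-screen GAS-10 remains comparable between visits as far as that day's order goes, so between-visit anxiety change is not invalid as a whole. The first-visit cross-tabulation of SCREEN against Qmci is not affected by the handouts.

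**What to change.** 1. Keep all test pairs. Estimate the SCREEN and Qmci ICCs from a mixed model with patient as a random effect and screen order as a fixed effect.
2. Include first-screen identity in every post-screen and pre-post GAS-10 contrast. The pre-screen contrast needs no such term.
3. Describe the all-patient SCREEN ICC as reliability under feedback; adjusting for order does not remove a feedback effect. Add sensitivity analyses by tailored-handout status, which follows from the recorded SCREEN result, and by the health change and MCI-related care already asked about at each visit. State that splitting on the first score restricts the range, so a lower ICC within a subgroup is not in itself evidence of a handout effect.

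The cost is analysis time and a few extra model terms. No new data are needed beyond the randomised order, which must be retrievable for each visit; the article does not say whether it was recorded.

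Any future collection could randomise order once per patient. That gives up the within-patient order contrast and still needs order in the model: left unadjusted, a fixed order counts the order effect as between-patient variance, and at d = 0.5 the ICC would read (0.85 + 0.0625)/1.0625 = 0.859. Whether handouts are given is not in question here.
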